### Sample size and sampling

#### Community quantitative surveys

For the community series of cross sectional surveys, we adopt the formula by Hemming et al. 2016 for cross sectional sample size determination for a stepped wedge study. To determine a moderate effect size of 0.3 (SD 1) for say change in Blood pressure at 5% significance, and detectable power of 88%, before and after the exposure to the intervention, given a sample size that is feasible and realistic in these setting, with four (4) steps and five (5) clusters per step, a total sample size of 50 participants per cluster is assumed reasonable [27]. However, assuming an intracluster correlation coefficient, r, of 0.01, a fixed cluster sample size, m = 50, survey rounds, t = 5 and a design effect of 2.93 [27] with 20 predetermined clusters; the required total sample size per survey round is 2930 households. We recognise that a random sample of household in a vast geographic setting can return a lot of non-responses. Thus, to cater for non-responding households and to avoid replacement of randomly selected eligible households, we factor in a non-response of 30% and generate the final household sample of 4000; with each cluster contributing 200 households. *Sampling households and participants*: The sampling frame for the surveys is generated through a mapping and listing exercise. All households in the catchment area are assigned a unique number to generate a sampling frame. A random sample of 200 eligible households with at least one adult per household is generated from the sampling frame using a random number generator. The selection is conducted by the study statistician. Study personnel (trained research assistants) approach the selected households for recruitment into the household/community survey. When a selected household is approached and has at least one eligible adult, study personnel describe the purpose of the study in the appropriate language, obtain participant consent and administer the study questionnaire and conduct anthropometric and blood pressure measurements using standardised and validated equipment. All eligible adults in the household aged 25–70 years are enrolled.

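### The final sample of 4000 households yields 2800, not the required 2930, at the stated 30% non-response (a minor error with no loss of power)

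*Protocol article*

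**What the plan says.** All the figures are in the protocol article, under Sample size and sampling, Community quantitative surveys. The calculation uses "a fixed cluster sample size, m = 50, survey rounds, t = 5 and a design effect of 2.93" and, "with 20 predetermined clusters", concludes that "the required total sample size per survey round is 2930 households".

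The section then expects many non-responding households in a large area. To allow for them, and "to avoid replacement of randomly selected eligible households", it states: "we factor in a non-response of 30% and generate the final household sample of 4000", "with each cluster contributing 200 households".

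The requirement, the non-response allowance and the final sample are all expressed in households. The same section says that all eligible adults aged 25 to 70 in a selected household are enrolled. It gives no average number of such adults per household.

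**The concern.** An allowance for non-response should leave the required number once the expected losses have occurred. The number to approach is therefore the requirement divided by the expected response proportion. Here the final sample, reduced by the plan's own 30%, falls below the plan's own requirement.

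What is at stake is the consistency of the sample size statement. Someone monitoring a survey round that achieved 2800 responding households, exactly as the 30% assumption predicts, could not tell from the article whether the round had met its plan or fallen short. Anyone rechecking the calculation would not arrive at 4000 by the standard formula.

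**Working it through.** **Inputs (all from Community quantitative surveys).** 50 participants per cluster, 20 clusters, design effect 2.93, requirement 2930 households per round, non-response 30%, final sample 4000 households, 200 per cluster.

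**1. The plan's base figure reproduces.** 50 x 20 x 2.93 = 2930, or 2930/20 = 146.5 per cluster. The final sample also agrees with its per-cluster figure: 20 x 200 = 4000.

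**2. Yield of the final sample at 30% non-response.**
- 4000 x (1 - 0.30) = 2800 responding households, or 140 per cluster.
- Shortfall: 2930 - 2800 = 130 households per round; 130/2930 = 4.4%.
- Over five rounds: 5 x 130 = 650.

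**3. Sample that would preserve 2930.**
- 2930/0.70 = 4185.7, so 4186 households, or 209.3 per cluster.
- With equal whole-number clusters: 210 x 20 = 4200, which yields 4200 x 0.70 = 2940.

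**4. Non-response that 4000 does cover.** 1 - 2930/4000 = 0.2675, or 26.75%.

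**5. Where 4000 probably comes from.** 2930 x 1.3 = 3809, or 190.45 per cluster. Rounding up to 200 per cluster gives 4000. The article does not state this route, so it is an inference. Multiplying by 1.3 alone would have left 3809 x 0.70 = 2666 households, about 264 short. The rounding adds (4000 - 3809) x 0.70 = 134 responders, and the remaining gap is 130.

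**6. Does the gap matter for power?** I used the Hussey-Hughes variance for a cross-sectional stepped wedge. The plan gives 20 clusters, 4 steps, 5 survey rounds, SD 1, an effect of 0.3 SD, 5% significance and "assuming an intracluster correlation coefficient, r, of 0.01". Sidedness is not stated, so I assume two-sided. With m participants per cluster and round, s2 = (1 - 0.01)/m and t2 = 0.01. With I = 20 clusters and T = 5 rounds, the design sums are U = 50, W = 750 and V = 150:

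variance = I s2 (s2 + T t2) / [(IU - W) s2 + (U^2 + ITU - TW - IV) t2] = 20 s2 (s2 + 0.05) / [250 s2 + 750 x 0.01]

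- m = 10 (50 per cluster over five rounds): power for 0.3 SD = 88.0%, which is the plan's stated power.
- m = 140: s2 = 0.00707, SE = 0.0295, power above 99.9%. Effect detectable at 88% power: (1.960 + 1.175) x 0.0295 = 0.093 SD.
- m = 146.5: power above 99.9%. Detectable effect 0.091 SD.

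The last two lines count one household as one independent participant.

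**7. Individuals instead of households.** 2800 households reach 2930 individuals once they average 2930/2800 = 1.046 enrolled adults. The true average is not given. Assumed values give 2800 individuals at 1.0 per household, 2940 at 1.05, 4200 at 1.5 and 5600 at 2.0.

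**The case against.** The best defence is that 4000 is a rounded, practical number. The authors probably added 30% to 2930 and rounded up to a convenient 200 per cluster, so the total is neither arbitrary nor unexplained. This is plausible and softens the point. It does not remove it, because adding 30% does not preserve the requirement after 30% is lost, and the rounding recovers only about half of the difference.

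A second defence is that the base of 2930 is derived from 50 participants per cluster and only then labelled households. Several adults may be enrolled per household, so the number of people measured could pass 2930 with 2800 households. This also stands as a possibility, and the threshold of 1.046 adults per household is low. It does not make the household statement correct as printed. The mismatch of units is a separate question.

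A third is that effectiveness is a secondary outcome and the article describes its core analyses as qualitative, so a 4.4% gap has little weight. I accept this for the grading.

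Three stronger readings are tempting, and the documents do not support them:
- *The study is underpowered.* It is not. On the plan's own assumptions the stated 88% power for 0.3 SD is already reached with 10 participants per cluster and round, far below 140.
- *The shortfall cannot be recovered because replacement is forbidden.* The article gives avoiding replacement as a reason for enlarging the sample. It does not state a ban.
- *Every round will fall short.* That follows only for households and only if non-response really is 30%. At 26.75% or less, the target is met.

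**Conclusion.** The statement is wrong as written, and the error is minor. A final sample of 4000 households does not deliver 2930 per round at 30% non-response. It delivers 2800, which is 130 (4.4%) fewer, and the sample that would preserve 2930 is 4186. This part rests only on figures printed in one section and needs no outside assumption.

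The explanation (x 1.3, then rounding to 200 per cluster) is likely but inferred. The conclusion that power is unaffected rests on the Hussey-Hughes model, the plan's intracluster correlation of 0.01, two-sided 5% significance and one independent participant per household. The margin is wide: 140 per cluster and round against the 10 that give 88.0%. A reader should take from this an inconsistent non-response allowance, not a sample that is too small for its purpose.

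**What to change.** Correct the sentence and leave the fieldwork as it is. Either wording will do:

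- Keep 4000 households and the 30% allowance, and state the expected yield as about 2800 responding households per round (140 per cluster). This is the cleaner choice, since it leaves the planning assumption alone.
- Keep 4000 and 2930, and state that 4000 covers the target only up to 26.75% non-response. Present this as the tolerance of the chosen sample, not as a new forecast of non-response.

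If a detectable effect is added (about 0.093 SD at 88% power with 140 per cluster and round), name the Hussey-Hughes model, the intracluster correlation of 0.01 and two-sided 5% significance. Say also that it assumes one independent participant per household.

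The cost is one edited sentence. Raising the sample to 210 per cluster (4200) would also restore 2930, but it would add 200 households per round. The power check gives no reason to spend that.

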#### Health facility surveys

All Health centre IIIs are assessed for readiness and capacity to provide care for CVD prevention and control. The assessment is conducted with a quantitative questionnaire adapted with modification from the World Health Organisation service availability and readiness assessment (SARA) instrument. The tool is administered to the facility/unit heads to capture the relevant information on CVD prevention, service availability and readiness and staffing. In addition, health workers’ knowledge, practices and attitudes are assessed to generate relevant skill and knowledge gaps during pre and post training assessments using a health workers questionnaire. All health workers enrolled for training participate in these evaluations. Furthermore, a purposive sample of health workers participate in qualitative evaluations to assess organizational readiness for change, including perceived barriers to change, acceptability, feasibility, and appropriateness of implementing the enhanced program at the health facility. The required sample size is informed by the principal of data saturation in qualitative research. For readiness of the community component, CHWs are assessed with a questionnaire to document their current knowledge, practices and attitudes on prevention of CVDs. In addition, perceived barriers to change, acceptability, feasibility, and appropriateness of implementation is explored qualitatively to garner CHWs perspectives. We also plan to conduct focus group discussions with community members and key informant interviews to assess community attitudes, perceptions, acceptability and appropriateness of community interventions and strategies. Similarly, an appropriate number of FGDs is determined based on principle of information saturation, geographical diversity, age distribution and gender and other parameters deemed relevant. ***Patient surveys*** – To generate information on the health status of the patients, quality of life, satisfaction, challenges, adherence practices and support mechanisms, proportion of screened patients at health facilities, a survey of patients is conducted using a patient assessment questionnaire.

## Study outcomes and evaluation framework

### Primary outcome

Implementation (Reach, Appropriateness, Acceptability, Self-efficacy, Adoption, Cost, Feasibility, Fidelity and Sustainability).

### Secondary outcome

Effectiveness (Change in selected profiles e.g. knowledge, blood pressures, waist hip ratio/BMI, alcohol history, smoking status, quality of life, etc.).

#### Evaluation frameworks

We propose to evaluate the project guided by two validated and widely used implementation frameworks 1) RE-AIM, an evaluation framework and 2) the Consolidated Framework for Implementation Research (CFIR), a determinant framework [28–32]. The broader implementation outcomes as proposed by Proctor and colleagues [33] —acceptability, adoption, appropriateness, feasibility, fidelity, implementation cost, coverage, and sustainability are pre-determined in order to understand the factors affecting the implementation, the processes, and the accruing results. The RE-AIM and CFIR frameworks are selected based on a review of literature that demonstrate that they are suitable for a complex intervention. The RE-AIM (Reach, Effectiveness, Adoption, Implementation and Maintenance) framework offers a comprehensive structure designed to systematically assess the robustness of interventions across settings and individual subgroups and the potential for their scaling up and spread to additional settings [30]. Reach, the percent and representativeness of individuals willing to participate; Effectiveness, the impact of the intervention on targeted outcomes and quality of life; Adoption, the per cent and representativeness of settings and intervention staff that agree to deliver a program; Implementation, the consistency and skill with which various program elements are delivered by various staff; and Maintenance, the extent to which individual participants maintain behaviour change long term and, at the setting level, and the degree to which the program is sustained over time within the organizations delivering it (www.re-aim.org). The CFIR is an implementation framework that allows for systematic evaluation of barriers and facilitators that may impact the adoption, implementation, and/or maintenance of a program [34–36]. It provides a useful template for organizing key concepts in implementation research. A detailed description of the framework is available elsewhere [34, 36]. Some elements of this framework will be used to guide data collection (both qualitative and quantitative), and analysis of the contextual factors that have potential to impact the implementation of the project. The CFIR Research Team provides resources to guide implementation evaluation (https://cfirguide.org/). In Table 1 we present a detailed process evaluation guide checklist that we have adopted with modifications of the frames to measure the delivery of the intervention and the evaluation process. Pre-implementation, implementation and post implementation processes of the intervention are foreseen using mixed methods [28].

**Table 1 Tab1:** Evaluation framework for both the Community/Health facility Strategy

Primary outcomes - (Reach, Appropriateness, Acceptability, Self-efficacy, Adoption, Cost, Feasibility, Fidelity and Sustainability)			
Implementation outcome	Description	Measurement	Time points
Reach	Proportion of the health care/community providers/target population approached; Uptake of intervention packages; and proportion of adherent	Analysis of routine data generated by CHW, peers & Health facilities and individual/patients quantitative assessments using household/patient questionnaires	0, 6, 12, 18 and 24 months
Appropriateness	The extent to which proposed interventions can be delivered at health facilities/community	Individual interviews Focus group discussion, Key informant interviews	0, 6, 12, 18 and 24 months
	Organizational Readiness	Availability and functionality of infrastructure including personnel, equipment, supplies etc. measured using the Health facility readiness and capacity assessment questionnaire	0, 6, 12, 18 and 24 months
	Linkage to healthcare	1. Self-report using h/h questionnaire, 2. Data extraction checklist	12 and 24 months
	Referrals for task sharing/shifting	Data extraction checklist	12 and 24 months
Acceptability	User and provider feedback	Focus group discussions guides Key informants	Formative process ongoing
	Individual/Patient satisfaction (Needs)	Patient Satisfaction Questionnaire	12 and 24 months
Self-efficacy	Personnel beliefs about own competencies to achieve implementation goals	Provider questionnaire Pre/post training assessment tools	12 and 24 months
Adoption	Implementation of the project and challenges to implementation (Barriers and opportunities and coping mechanisms).	Focus group discussions and individual interviews Key informant interviews	0, 6, 12, 18 and 24 months (formative process ongoing)
Cost	Costs associated with implementing the packages	Checklists for cost data (Health facility cost data related to the project Community program cost data)	12 and 24 months
Feasibility	Exposure to and retention of the enhanced interventions e.g. CVD education, counseling etc.	Data extraction checklist (Daily activities conducted related to the enhanced interventions e.g. counselling, no. of people profiled, followed up etc.)	12 and 24 months
Fidelity	The extent to which providers are delivering packages as per the protocol/guidelines	Observer rating forms	Formative process ongoing
Sustainability	The extent to which the program is being implemented as a standard of practice	Key informant interviews with providers.	12 and 24 months
Secondary outcomes – Effectiveness (Change in selected profiles e.g. knowledge, blood pressures (diastolic blood pressure), waist hip ratio/BMI, alcohol history, smoking status, etc.) measured at T 0,6,12,18 and 24 month using surveys.			

### Data management and quality control

The study coordinator will be responsible for all data collection instruments and their transportation to and from the study sites in Mukono and Buikwe and back to Makerere University School of Public Health (MakSPH). The study instruments are either paper based or electronic collected with android enabled phones and tablets using REDCap. All data (paper based or electronic) before submission to MakSPH is field edited for accuracy and consistency. Clean electronic data will be synchronized by the field team and uploaded to the MakSPH server on a daily basis. All qualitative data will be audio recorded and transcribed verbatim and then securely stored at MakSPH. Qualitative audio transcript shall also be edited, coded and analysed at MakSPH. Completed paper based forms shall be converted to electronic through data entry at MakSPH. To ensure quality of data collected, the coordinator is supported by two field supervisors/data quality controllers to provide day to day support and supervision of the data collection exercise. The supervisors check progress and quality of work, clarify questions on study instruments, and supply additional study instruments and stationery, and advice on how to solve logistical problems. Further quality assurance and fidelity checks are conducted by the study investigators on a monthly or more regular basis.

### Data analysis

Qualitative data will be analysed using the framework analysis technique, which facilitates thematic analysis.

The quantitative analyses will be guided by the principle of intention-to-treat and clusters analysed according to their randomised crossover time irrespective of whether crossover was achieved at the desired time. The analysis will be conducted in Stata or R Software. Initially, descriptive analysis (before and after) will be conducted and categorical data presented using counts and percentages, while continuous variables presented using measures of central tendencies. No multiple imputations will be conducted for missing data. The following descriptive are envisioned.Reach of the project, captured through: the number and percentage of providers and individuals enrolled into the project at the community and health facility levels; the number of individuals partaking and adhering to the recommended interventions at the various levels.Effectiveness: Activities and clinical endpoints will be used to assess effectiveness of the project at selected intervals observed longitudinally. The measures include: the proportion of project activities (community/health facilities) achieved at any point in time; change in clinical profiles e.g. blood pressures, BMI, alcohol history, smoking status, quality of life etc., achieved at 0, 6, 12, 18 and 24 months; and proportion of completers and attritors.Adoption: The number/percentages of individuals/providers approached or agreed to take part in the intervention (s) and proportion of individual providers (CHW, Peers or NPHW) that deliver the intervention.**I**mplementation: Captured by detailed description of the contextual adaptations of the project, the time required for intervention, and the costs of the intervention. Implementation information including process, facilitators and barriers, costs, and contextual issues will be analysed descriptively and qualitatively. Readiness of implementation (Available resources) – BP monitoring devices, Weighing scales, Stadiometers, measuring tapes, Glucometers and strips, first line antihypertensive drugs, guidelines, personnel, space, time etc. will be descriptively described and presented using graphs. Quality and quantity of equipment and their functionality, supplies and other necessary infrastructure will be descriptively analysed. Fidelity – Evidence of use of guidelines and protocols/simplified algorithm and any iterations recorded will be analysed descriptively and qualitatively. Costs - Costs associated with implementing the packages. Monetary requirements for each intervention (community and health facility based) will be analysed descriptively as a measure of sustainability based on feedback reports from community members, patients, CHWs, health unit staff and project and field coordinators.Maintain: The extent to which the project becomes part of routine practice and policy will be explored. Evaluation of maintenance will include the following: Analysing the proportion of health providers who are introduced to the enhanced approach and those adapting the strategies.

Paired t-tests will be run to compare means across clusters and within clusters. However, given the time trend and clustering effects, we proceed to adjust for different observation periods and for clustering in the data by fitting an appropriate generalised linear mixed model or using generalised estimating equations. For continuous (and normally distributed) outcomes, we fit a linear model with random effect for cluster and fixed effect for each step; and, for binary outcomes, a logistic regression model with random effect for cluster and fixed effect for each step.

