### Evaluation plan

To evaluate the study, we propose to conduct a series of cross-sectional surveys every 6 months at time (T) 0, T6, T12, T18 and T24 at the community and health facility levels. We assess with key community and household members, health facilities, health workers, and patients. The evaluations uses both: qualitative assessments – to evaluate the process, barriers and opportunities; and quantitative measurements – to assess effects and process outcomes. During the interventions, formative processes (process evaluations) and detailed documentation of process, costs and activities take place.

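### Paired t-tests on serial cross-sectional surveys have no person-level or across-cluster pairing to rest on, and before-after pairing of cluster means counts any time trend as effect

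*Protocol article*

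**What the plan says.** The Evaluation plan describes the data source: "a series of cross-sectional surveys every 6 months at time (T) 0, T6, T12, T18 and T24". Under Community quantitative surveys, the sample size rests on a formula "for cross sectional sample size determination for a stepped wedge study", and households are drawn at random from a listing.

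Under Data analysis, the article first announces summaries: "Initially, descriptive analysis (before and after) will be conducted". It describes effectiveness measures as taken "at selected intervals observed longitudinally" and, in the same item, lists the share of people who complete and who drop out. After the descriptive list it adds: "Paired t-tests will be run to compare means across clusters and within clusters". The next sentence reads: "However, given the time trend and clustering effects, we proceed to adjust for different observation periods and for clustering in the data". For continuous outcomes it then says: "we fit a linear model with random effect for cluster and fixed effect for each step".

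The article does not name the unit that is paired, does not label the t-tests as descriptive, and does not say which result governs if the t-tests and the model disagree.

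**The concern.** A paired t-test needs two measurements on the same unit, or on units matched by design. Serial cross-sectional samples do not supply this for people, and nothing in the article matches one parish to another. That leaves the cluster mean before and after crossover. In a stepped wedge every cluster moves from control to intervention and never back, so its exposed rounds are always later than its control rounds. A paired test has no term for time, so any secular change enters the estimate as if it were the effect of the programme.

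At stake is an unadjusted p-value printed beside the model result. If the two differ, a reader has no stated rule for choosing, and the unadjusted figure can mislead in either direction.

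**Working it through.** **Inputs from the article.** There are 20 clusters in 4 sequences of 5, surveyed at months 0, 6, 12, 18 and 24, with the baseline survey before the intervention starts. The ICC is 0.01, the SD is 1 and the required sample is 2930 per round. Per cluster-round: 2930/20 = 146.5.

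**Assumptions.** The article gives no size for the trend. I take linear drifts of 0, 0.01, 0.02 and 0.03 SD per six-month round, a two-sided 5% test, no true intervention effect, and independent sampling error between rounds once the cluster effect is removed. The article states no error rate for the t-test, so there is no figure of its own to reproduce.

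**Step 1: time gap.** For a cluster that crosses over after s rounds:

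| s | Mean month before | Mean month after | Gap |
|---|---|---|---|
| 1 | 0 | 15 | 15 |
| 2 | 3 | 18 | 15 |
| 3 | 6 | 21 | 15 |
| 4 | 9 | 24 | 15 |

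All-before against all-after therefore gives 15 months (2.5 rounds) in every sequence. Last control round against first exposed round gives 6 months (1 round). T0 against T24 gives 24 months (4 rounds).

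**Step 2: standard error of the mean of 20 paired differences.** The sampling variance of one cluster-round mean is 0.99/146.5 = 0.006758; the cluster effect cancels in the difference.

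- Adjacent rounds, and T0 against T24: variance 2 × 0.006758 = 0.01352; SE = √(0.01352/20) = 0.0260.
- All-before against all-after: the factor 1/s + 1/(5−s) is 1.25, 0.833, 0.833 and 1.25, mean 1.0417; variance 0.00704; SE = √(0.00704/20) = 0.0188.

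**Step 3: false rejection.** Bias = rounds apart × drift per round. The rejection probability comes from the noncentral t with 19 df and noncentrality bias/SE. At 0.02 SD per round the noncentralities are 0.02/0.0260 = 0.77, 0.05/0.0188 = 2.67 and 0.08/0.0260 = 3.08.

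| Drift per round (SD) | Adjacent rounds | All-before vs all-after | T0 vs T24 |
|---|---|---|---|
| 0 | 5% | 5% | 5% |
| 0.01 | 6.5% | 24% | 31% |
| 0.02 | 11% | 72% | 83% |
| 0.03 | 20% | 97% | 99% |

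A direct simulation agrees with these figures to within about half a percentage point.

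**Step 4: sensitivity, all-before against all-after.** With 50 people per cluster-round the figures at 0.01, 0.02 and 0.03 SD are 12%, 32% and 60%. With 146.5 per cluster-round and a cluster autocorrelation of 0.8 (SE 0.0214) they are 20%, 60% and 92%.

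**Step 5: the planned model.** In simulation with no true effect, a model with random cluster, fixed step and an intervention indicator (variance components taken as known) gave a mean estimate of 0.00 and a type I error of about 5% at every drift tried, from 0 to 0.10 SD per year.

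**The case against.** The strongest reply is that the article already deals with this. Straight after the t-tests it concedes trend and clustering and moves to an adjusted model that holds its level. No sentence rests an effectiveness conclusion on the t-tests; effectiveness is a secondary outcome, and the Study design section calls the core analyses qualitative. This stands, and it limits the harm. It does not remove it, because the tests are still planned and their status is not stated.

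Several stronger readings are tempting, but the article does not support them:

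- **Every before-after pairing carries 15 months of trend.** It does not. That gap belongs to one choice of rounds; the range is 6 to 24 months and the article fixes none.
- **The test is invalid outright.** On 20 cluster means it holds about 5% when there is no trend. The fault is bias under a trend, and the article gives no size for one.
- **The rising burden in the Background shows which way the error goes.** That passage reports rising cases at health facilities, not a drift in mean blood pressure among sampled households. If mean pressure did rise, the before-after test would tend to hide a benefit.
- **New households are certainly drawn each round.** The article does not say so, and the Study design section speaks of repeated measures at household and patient level. That wording sits badly with the cross-sectional plan but describes no linkage of records.
- **Paired tests have no place anywhere in this trial.** Health workers are assessed before and after training, and the same facilities are assessed repeatedly. Pairing can be legitimate there.

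A journal article may also leave the unit of pairing to a fuller document. That excuses the missing detail, but not a stated test that does not suit the survey design.

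**Conclusion.** The point holds for survey-based effectiveness outcomes. Pairing people or pairing across clusters has no basis in the design described, and pairing cluster means before and after crossover is biased whenever outcomes drift over time, a possibility the plan itself concedes. The size depends on two things the article does not fix: the drift and the rounds paired. At an assumed 0.02 SD per round, false rejection runs from 11% to 83% across the three pairings; with no drift it is about 5%. Severity is minor to moderate: the time- and cluster-adjusted analysis is already planned, so the risk is an unadjusted p-value beside it, not a wrong main analysis.

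**What to change.** - For survey-based effectiveness outcomes, remove the paired t-tests and present cluster-by-round means and plots without p-values.
- State that the time- and cluster-adjusted mixed model, or the GEE alternative, is the sole inferential analysis for these outcomes.
- Keep paired tests only where the same unit is measured twice with linked records, such as health workers' scores before and after training, and name that unit.
- Reconcile the phrase "at selected intervals observed longitudinally" and the reporting of completion and dropout with the cross-sectional design of the community surveys, or say which components they refer to.

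The cost is a few sentences in the analysis section. No data, design feature or sample size changes.
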